## Abstract

**Background:**

Currently, the standard curative treatment for ventricular tachycardia (VT) and ventricular fibrillation (VF) is radiofrequency catheter ablation. However, when the VT circuit is deep in the myocardium, the catheter may not be delivered, and a new, minimally invasive treatment using different energies is desired.

**Methods:**

This is a protocol paper for a feasibility study designed to provide stereotactic radiotherapy for refractory VT not cured by catheter ablation after at least one catheter ablation. The primary end point is to evaluate the short-term safety of this treatment and the secondary endpoint is to evaluate its efficacy as assessed by the reduction in VT episode. Cyberknife M6 radiosurgery system will be used for treatment, and the prescribed dose to the target will be 25Gy in one fraction. The study will be conducted on three patients.

**Conclusion:**

Since catheter ablation is the only treatment option for VT that is covered by insurance in Japan, there is currently no other treatment for VT/VF that cannot be cured by catheter ablation. We hope that this feasibility study will provide hope for patients who are currently under the stress of ICD activation.

**Trial registration:**

The study has been registered in the Japan Registry of Clinical Trials (jRCTs042230030).

## Introduction

Sustained ventricular tachycardia (VT) and ventricular fibrillation (VF) are arrhythmias that significantly reduce blood circulation and cause sudden cardiac death.

Treatment of patients with VT involves electrical cardioversion or implantable cardioverter defibrillator (ICD) implantation followed by administration of medication. Specially in patients with recurrent ventricular arrhythmias, it is essential to wear an ICD to continuously monitor cardiac activity and to restore a normal pulse with an electrical defibrillator when VT or VF is detected. Although ICD therapy is considered the most reliable treatment for preventing sudden death, frequent VT attacks and electroshock therapy with ICDs have been reported to worsen patients’ quality of life and long-term prognosis.
^
1
^
^,^
^
2
^

Currently, the standard curative treatment for VT and VF is radiofrequency catheter ablation with a three-dimensional (3D) mapping system. The conventional ablation therapy involves ablation from the endocardial side; however, in the case of ablation of the VT, ablation from the epicardial side may be performed depending on the thickness and location of the myocardial tissue to be ablated. However, a previous study has reported that more than half of the VT cases after myocardial infarction or other congenital cardiac diseases recur within one year of ablation.
^
3
^ Furthermore, although catheter ablation therapy clearly reduces the recurrence rate of VT, improvement in life expectancy remains unconfirmed. A key factor is the high recurrence rate, and improvements in treatment techniques are warranted.

The causes of tachyarrhythmia include arrhythmias due to abnormal automaticity and re-entry through the tachycardia circuit. To interrupt the tachycardia circuit, catheter ablation is performed as a curative treatment for arrhythmias caused by re-entry. Catheter ablation generates Joule heat in the myocardial tissue around the catheter electrode and cauterizes the tissue, thereby interrupting the tachycardia circuit. However, when the VT circuit is deep in the myocardium, under epicardial fatty tissues, or near the coronary arteries, the catheter may not be delivered, and a new, minimally invasive treatment using different energies is desired.

Since 2014, several case reports on stereotactic radiotherapy for VT have been published.
^
4
^
^–^
^
9
^ A systematic review published in 2021 revealed the safety and short-term reduction in sustained VT/VF burden.
^
10
^ To implement this method in Japan, the technique needs to be converted to one that can be implemented in Japan, and the safety of the method should be clarified in Japanese patients.

This study aimed to convert the results of overseas research into a feasible method in local practice and to verify whether radioablation using stereotactic radiotherapy techniques for patients with VT not cured by catheter ablation can reduce the number of VT occurrences compared to before radioablation treatment and whether the use of antiarrhythmic drugs can be reduced.

## Protocol

### Study design and patient eligibility

This prospective, single-arm, single-center study was approved by the Nagoya University ethics committee (CRB4180004) and registered to the Japan Registry of Clinical Trials (jRCTs042230030). Patients who are refractory to at least one catheter ablation and had received one or more anti-arrhythmia drug treatment with over three episodes of VT episode with therapeutic intervention (anti-tachycardia pacing (ATP) or shock) in the last three months are considered eligible to participate in the study. Because data from Asian countries are very limited, we will first design a feasibility study at a single center. The inclusion criteria are as follows: age of ≥18 years; received antiarrhythmic drug treatment after ICD implantation; with recurrent VT after at least one catheter ablation; have experienced ≥3 VT attacks within the past three months while taking at least one antiarrhythmic drug; with VT that cannot be treated with catheter ablation; without history of cardiac irradiation; and provided written informed consent.

Meanwhile, the exclusion criteria are as follows: with heart failure requiring a left ventricular assist device; with a low probability of survival of >6 months because of factors other than VT; with contraindications for irradiation; undergoing maintenance hemodialysis or peritoneal dialysis; with organic heart disease requiring surgery; with acute coronary or heart disease requiring hospitalization; at a high risk of radiation pneumonitis (e.g. idiopathic pulmonary fibrosis); with difficult-to-control pericardial or pleural effusions; having difficulty in resting in supine for 1 h; and with other illnesses or reasons that make it difficult to perform necessary examinations or follow-up investigations, or for which the principal investigator/participating physician determines that the patient is unfit to participate in this study. The discontinuation criteria are as follows: withdraws consent, or no longer meets the eligibility criteria while on the treatment waiting list, or difficult to continue the research due to an adverse event, or Accredited Clinical Research Review Committee instructs to discontinue the research, or the principal investigator/participating physician determines that the patient is unfit to participate in this study.

Any additional standard treatment of VT is acceptable. Changes in medication will be always monitored during the study. Medications will not be restricted if necessary. However, medications will be monitored throughout the study even if they are not considered directly relevant to the study.

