### Endpoints

The primary endpoint is the short-term safety of the treatment. Safety evaluations will be performed on days 0, week 2, 1 month, 1.5-month, 2 month, 3 month, 4 month, 5 month, 6 month, 9 month, and 12 months after treatment. Myocardial dysfunction (e.g., contractility, diastolic dysfunction, pericarditis, pericardial effusion, myocardial ischemia, and heart failure), lung injury, and other treatment-related acute and subacute (up to 6 months after irradiation) complications greater than G3 in the Common Terminology Criteria for Adverse Events ver. 5.0 will be monitored. The secondary endpoint is the efficacy of the treatment. Cardiac function assessed by imaging, reduction of VT treatment (ATP and/or shock) by ICD, presence of dose reduction of antiarrhythmic drugs, overall survival, and patient quality of life will be measured using the 36-Item Short Form Survey and EuroQol-5D. Data collected for assessment of endpoints are as shown in
Table 1. All data are registered to Research Electronic Data Capture (REDCap) at required timing as described previously. As this is the first treatment of VT using CyberKnife in Japan, we will evaluate the safety and efficacy of the treatment in three patients. If a patient enrolled in the study is not treated after enrollment, the patient is not counted, and individual enrollment will be continued until three eligible cases are treated. The enrollment will be terminated upon accumulation of three eligible cases.

**Table 1. T1:** Timing and exams of follow up.

	Base line	Day0	Wk2	1M	1.5M	2M	3M	4M	5M	6M	9M	12M
ICD record (ATP and Shock)	○	○	○	○	○	○	○	○	○	○	○	○
Holter ECG (24hr)	○	○		○			○			○		○
Echocardiography	○			○			○			○		○
12-lead ECG	○		○	○	○	○	○	○	○	○	○	○
Blood test	○	○	○	○	○	○	○	○	○	○	○	○
Chest CT	○						○			○		○
Chest Xp	○	○		○		○		○	○		○	
Cardiac MRI	○			○								○
Myocardial scintigraphy	○			○								○
QOL check	○			○								○
Adverse event		○	○	○	○	○	○	○	○	○	○	○

ECG: electrocardiogram, ATP: anti-tachycardia pacing.

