### Study plan

*Target delineation and planning*

Patients will undergo expiratory and inspiratory breath-holding and respiratory-gated contrast-enhanced computed tomography (CT) to create a stereotactic body radiotherapy (SBRT) plan. A 3D map from the electroanatomic mapping system (CARTO; Biosense-Webster, Israel) and ECG-gated CT scan will be fused to the planning CT to locate the target region and calculate the motion according to the heartbeats. The precision treatment system and CyberKnife M6 radiosurgery system (both from Accuray Inc., USA), which contain Synchrony, a respiratory compensation technology, are used to plan and deliver the planned dose.
^
11
^ Positron emission tomography/CT and contrast-enhanced magnetic resonance imaging could be used as secondary reference images. ICD leads are used for respiratory tracking. A 3-mm planning target volume (PTV) margin will be added to the target, and a dose of 25 Gy will be delivered to the PTV in a single session. The dose constraints are listed in
Table 2. The PTV margin can be varied to account for setup errors and motion uncertainty, and the PTV dose can be reduced to 20 Gy to prioritize dose constraints for organs at risk. The maximum allowable dose is 32.5 Gy.

**Table 2. T2:** Dose constraints.

Organ at risk	Max dose	Volume recommendation
trachea	20.2 Gy	V10.5 Gy < 4 cc
esophagus	15.4 Gy	V9 Gy < 5 cc
stomach	12.4 Gy	V11.2 Gy < 10 cc
aorta	25 Gy	<20 Gy preferred if possible
lung	-	V7.4 Gy < 1000 cc V7 Gy < 1500 cc
heart (exclude PTV)	25 Gy	V16 Gy < 15 cc Or D50% < 5 Gy
rib	30 Gy	V22 Gy < 1 cc
colonary artery	25 Gy	<14 Gy preferred if possible
atrium	4.4 Gy	preferred if possible
valve	10 Gy	Secondary: <25 Gy
spinal canal	8 Gy	
skin	14.4 Gy	V10 Gy < 10 cc
ICD	0.5 Gy	Does not allow the beam to pass through the ICD body

*Treatment*

The treatment as an inpatient procedure for at least 24 h after irradiation will be performed by a cardiologist and a radiation oncologist. During treatment, the ICD will be turned off, while the ECG will be carefully monitored by a cardiologist. The ICD will be turned on after completion of irradiation following an equipment check.

After treatment, a planned follow-up will be performed as described in the endpoint section.

*Quality control and quality assurance*

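### Two discontinuation criteria are not limited to the time before the single irradiation, so an adverse event can end the follow-up that measures the primary safety endpoint

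*Protocol article*

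**What the plan says.** The article (Study design and patient eligibility) lists five grounds for discontinuation: withdrawal of consent, loss of eligibility before treatment, an adverse event, an instruction from the Review Committee, and the physician's judgement. Three of them matter here:

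- Loss of eligibility, which is tied to the pre-treatment period: "no longer meets the eligibility criteria while on the treatment waiting list".
- Adverse event, with no time limit: "difficult to continue the research due to an adverse event".
- Physician's judgement, with no time limit: "the principal investigator/participating physician determines that the patient is unfit to participate in this study".

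Under Study plan, "a dose of 25 Gy will be delivered to the PTV in a single session". Under Endpoints, "The primary endpoint is the short-term safety of the treatment", and what is monitored includes "treatment-related acute and subacute (up to 6 months after irradiation) complications greater than G3 in the Common Terminology Criteria for Adverse Events ver. 5.0". The visit schedule begins "Safety evaluations will be performed on days 0, week 2, 1 month, 1.5-month, 2 month, 3 month, 4 month, 5 month, 6 month, 9 month"; its last visit is at 12 months. Table 1 has adverse events recorded at every visit from day 0 onward. On sample size, "we will evaluate the safety and efficacy of the treatment in three patients". The only rule on who is left out of the count concerns patients who enrol but are never treated.

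**The concern.** In a trial with a continuing treatment course, an adverse-event criterion normally stops the treatment while observation goes on. Here nothing of the protocol treatment remains to be stopped once the session is over, and the criterion is worded for the research as a whole. For a treated patient, an adverse event is therefore both the outcome of interest and a stated reason to leave the study that records it. Patients lost this way would not be a random subset, because they leave on account of their safety experience. With three patients, each one is a third of the data.

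**Working it through.** The article gives no sample-size formula, error rate or safety threshold, so there is no figure to reproduce. The check is a reading of the text, a visit count and an illustration.

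**1. What each open-ended ground can stop.** Before irradiation, either ground can stop a patient from being treated. That is reasonable, and such a patient is replaced under the enrolment rule. After irradiation there is no further session, so either ground can stop only follow-up. One item in the same list is confined to the waiting period and these two are not, so their wording reaches treated patients.

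**2. What would be lost, by type of trigger.**
- Trigger treatment-related and above grade 3: it has already been seen and recorded. An endpoint based on the first qualifying event loses nothing. The later course, survival and ICD records remain exposed.
- Trigger of lower grade: it does not qualify. Read literally, above grade 3 means grade 4 or 5, so even a grade 3 trigger falls here. If the patient then worsens, or has a different qualifying complication before month 6, that event comes after discontinuation.

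**3. Visits lost if observation ended at discontinuation.** The schedule is day 0, week 2, then months 1, 1.5, 2, 3, 4, 5, 6, 9 and 12. That is 11 visits, 9 of them from day 0 to month 6.

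| Last visit | Visits lost up to month 6 | Visits lost up to month 12 |
|---|---|---|
| Week 2 | 7 of 9 | 9 of 11 |
| Month 1 | 6 of 9 | 8 of 11 |
| Month 3 | 3 of 9 | 5 of 11 |

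**4. Illustration of the effect on the event rate.** All rates are assumptions; the article gives none. Let q be the share of patients discontinued after a lower-grade event, p1 the risk of a qualifying complication without such an event, and p2 the risk after one. Every event after discontinuation is taken as missed, and every treated patient stays in the denominator.

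- True rate = (1 − q)·p1 + q·p2
- Observed rate = (1 − q)·p1
- Chance of at least one event in three patients = 1 − (1 − rate)³

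With q = 20%, p1 = 10% and p2 from 10% to 50%:

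- True rate: 0.8 × 0.10 + 0.2 × 0.10 = 10%, up to 0.8 × 0.10 + 0.2 × 0.50 = 18%.
- Observed rate: 0.8 × 0.10 = 8%.
- Chance of at least one true event: 1 − 0.90³ = 27%, up to 1 − 0.82³ = 45%.
- Chance of at least one observed event: 1 − 0.92³ = 22%.

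The same calculation for other values of q:

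| q | True rate | Observed rate | Chance of ≥1 true event | Chance of ≥1 observed event |
|---|---|---|---|---|
| 10% | 10–14% | 9% | 27–36% | 25% |
| 20% | 10–18% | 8% | 27–45% | 22% |
| 33% | 10–23% | 6.7% | 27–55% | 19% |

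In this model the observed rate of qualifying complications is always too low. The size of the gap depends entirely on the assumed rates.

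**The case against.** The strongest reply has four parts.

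First, the adverse-event ground is conditional: it applies only where continuing has become difficult. A reader might infer that any adverse event removes a patient and that the primary outcome therefore censors itself. The text does not say so. This part stands.

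Second, a reader might infer that the study could report 0 of 2 when the truth is 1 of 3, with the exact two-sided 95% upper limit for zero events moving from 1 − 0.025^(1/3) = 71% to 1 − 0.025^(1/2) = 84%. The arithmetic is correct but the premise is not in the document. Only untreated patients are left out of the count, and a qualifying event that prompts discontinuation has already been observed, which gives 1 of 3. This part stands too. Nor does the article support a claim that VT burden would look better: later ICD data could be lost, but nothing shown fixes the direction.

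Third, rules on follow-up after discontinuation may be in the full protocol, which is not shown. That is true, and their absence from the article is not the point made here. The point is a rule the article does state, in terms wide enough to end follow-up of treated patients. The article does not say that data collection stops at discontinuation, and it does not say that it continues.

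Fourth, the two grounds may be meant mainly for the planning and waiting period. That is plausible, but then they should carry the limit that the neighbouring item carries.

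**Conclusion.** The point holds in a limited form. As written, the adverse-event and unfitness grounds permit, but do not require, the end of follow-up in a treated patient for reasons linked to the primary outcome. What can be lost is worsening or a later qualifying complication after a lower-grade event, together with later survival and ICD-therapy data. The triggering event and the patient's place among the three are not lost. An early stop is the costly case: 7 of 9 safety visits in the 6-month window if the last visit is week 2, and 6 of 9 if it is month 1. This assumes that observation ends with discontinuation, which the article leaves open. The illustrated shortfall, 8% observed against 10–18% true, rests on assumed rates and shows direction only. No figure in the article is wrong.

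**What to change.** - Limit the adverse-event and unfitness grounds to the period before irradiation.
- State that every treated patient stays in the safety analysis, and that adverse events, survival and ICD records are collected to 6 and 12 months unless the patient withdraws consent to data collection or the Review Committee stops the research. A patient too ill for a scheduled examination can miss it without leaving data collection.
- Report any incomplete follow-up with its date and reason.
- Do not count a patient who cannot complete visits as having had an endpoint event. The endpoint is confined to treatment-related complications above grade 3, and automatic imputation would bring in unrelated or milder events.

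This changes data collection and leaves clinical management alone. It costs a few sentences of protocol text, plus some effort to obtain records from sicker patients. The visits are already scheduled.

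### The secondary efficacy measures take no account of the added VT treatment that the protocol permits, so as worded they can be met without any benefit from radioablation

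*Protocol article*

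**What the plan says.** All references are to the protocol article.

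- **Design.** Study design and patient eligibility describes "This prospective, single-arm, single-center study". Endpoints fixes the number at three treated patients.
- **Aim.** The Introduction closes by asking whether radioablation "can reduce the number of VT occurrences compared to before radioablation treatment and whether the use of antiarrhythmic drugs can be reduced". This is a within-patient, before-after comparison credited to radioablation.
- **Co-treatment.** Study design and patient eligibility states "Any additional standard treatment of VT is acceptable" and "Medications will not be restricted if necessary", with no limit of time or type. It adds "Changes in medication will be always monitored during the study". The inclusion criteria require VT that catheter ablation cannot treat.
- **Endpoints.** "The secondary endpoint is the efficacy of the treatment"; short-term safety is primary. The efficacy measures include "reduction of VT treatment (ATP and/or shock) by ICD, presence of dose reduction of antiarrhythmic drugs". They are listed separately, and neither is conditioned on added treatment.
- **Unit.** The abstract's Methods paragraph says the study will "evaluate its efficacy as assessed by the reduction in VT episode". The eligibility paragraph speaks of VT episodes that received pacing or a shock. Endpoints speaks of the therapies delivered by the ICD.

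**The concern.** With no concurrent control, the only evidence of efficacy is the change from before to after irradiation. If drugs are added or raised in that period, the change mixes two causes. The ICD measure makes no distinction between them.

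The drug measure might be expected to act as a check, but it is worded as the presence of a reduction. It therefore has no category for an increase, and it can be met by substitution or by a reduction that is later reversed.

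At stake is whether the report can say that radioablation lowered VT burden. With three patients, one misread course is a third of the evidence. The Discussion hopes the study may guide clinicians, so the efficacy description will be read.

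**Working it through.** **Step 1. Score plausible courses against the two measures as worded.**

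| Course after irradiation | Fall in ICD therapies | Dose reduction present |
|---|---|---|
| A. Drugs unchanged, therapies fall | met | not met |
| B. Drug added or raised, therapies fall | met | not met |
| C. Regimen truly reduced, therapies fall | met | met |
| D. One drug lowered, another added, therapies fall | met | met |
| E. One drug lowered, later restored | depends on counts | met |

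A and B score identically, and so do C and D. A and C are the results the study hopes to show; in B and D the added drug may be the cause. The two measures together cannot separate them. Medication records could, but the stated measures do not draw on those records.

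**Step 2. Compare the units.** The abstract and the eligibility paragraph count episodes; Endpoints refers to ICD treatment. If one episode received three pacing bursts and one shock (an assumed example), it is 1 treated episode or 3 + 1 = 4 therapies. Nothing in the article says that bursts are summed, so this shows an ambiguity to settle and not a known error.

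**Step 3. Illustrate the size.** The plan has no efficacy figure to reproduce: it states no response rate, threshold or test. The inputs are:

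- three patients (Endpoints);
- baseline count b over three months: 3 is the minimum in the inclusion list, and 10 is assumed;
- radioablation effect exactly zero (assumed);
- co-treatment rate ratio RR over a later three-month window (assumed);
- true baseline rate equal to the observed count, so no regression to the mean (assumed).

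The chance that one patient shows a fall is P(X ≤ b − 1), where X is Poisson with mean b × RR. For all three patients it is that probability cubed.

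- b = 3, RR = 1: e^(−3) × (1 + 3 + 4.5) = 0.0498 × 8.5 = 0.423; cubed, 0.076.
- b = 3, RR = 0.5: e^(−1.5) × (1 + 1.5 + 1.125) = 0.2231 × 3.625 = 0.809; cubed, 0.529.

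| RR | b = 3: one patient / all three | b = 10: one patient / all three |
|---|---|---|
| 1 | 0.423 / 0.076 | 0.458 / 0.096 |
| 0.75 | 0.609 / 0.226 | 0.776 / 0.468 |
| 0.5 | 0.809 / 0.529 | 0.968 / 0.908 |
| 0.25 | 0.959 / 0.883 | 1.000 / 0.999 |

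(Cubes use unrounded values.)

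The result depends heavily on how many patients are co-treated. If only one of three is, at RR = 0.5, the chance that all three fall is 0.809 × 0.423 × 0.423 = 0.14 for b = 3 and 0.968 × 0.458 × 0.458 = 0.20 for b = 10. It also depends on the criterion. Requiring a fall of at least half in all three, with all three co-treated at RR = 0.5, gives 0.17 for b = 3 and 0.23 for b = 10.

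**The case against.** **The article gives no counting rule, and the full protocol or SAP may hold one.** This is correct, and the absence of a rule is not the point here. A reader might infer that the plan instructs analysts to count straight through rescue treatment; the article does not say so. What stands is the wording itself: an attribution to radioablation, free co-treatment, and a yes/no drug item that counts substitution as success.

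**Monitoring would reveal the problem.** A reader might infer that nothing in the design would show co-treatment at work. That is wrong. Medication changes are monitored throughout, and Table 1 schedules ICD records at baseline and 11 later time points, so with three patients the two can be set side by side. The objection removes the claim of concealment but not the gap between the data and the stated measures.

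**Repeat ablation is unlikely.** Entry requires VT that ablation cannot treat, so this is a minor route. Drug change is the main one.

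**Drug escalation works against the drug measure.** A pure increase does not score as a drug success. But course B still scores the same as an unchanged regimen, so the pair of measures does not identify rescue.

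**The units may mean the same thing.** The eligibility wording ties episodes to pacing or shock, and Endpoints can be read that way. One clarifying phrase would settle it.

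**Counting outcomes whatever else is given is a legitimate choice.** It is, but it describes radioablation plus whatever followed, which is not the aim as the Introduction puts it.

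**Conclusion.** The concern holds in a limited form. As worded, both efficacy measures can be met through co-treatment that the protocol permits: the ICD measure after drug intensification, and the drug measure through substitution or a transient reduction. The data that could show this are not tied to the measures.

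The primary safety objective is not affected, and no test or success threshold rests on the efficacy measures. A reader might take the probabilities above, or the fact that one patient in three is 33 percentage points, as a measured bias. They are not: baseline counts above 3, the rate ratios, the share of patients co-treated and the criterion of a fall in all three are assumptions, and the article defines no response rate. Within those assumptions, a co-treatment that halves the rate in every patient would make a uniform fall likely (0.53 to 0.91) with no radioablation effect. If only one patient is co-treated, the chance is 0.14 to 0.20, against 0.08 to 0.10 with none.

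**What to change.** None of these changes restricts care.

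1. **Name one counting unit.** Use ICD-treated VT episodes per month, which matches the eligibility paragraph and fits the ICD record in Table 1. Align the abstract and Endpoints to it, and report pacing and shock counts second. Counting untreated episodes as well would go beyond the pacing and shock record that Table 1 names.
2. **Report two rates for each patient.** Give the rate over full follow-up, and the rate up to the first antiarrhythmic increase, antiarrhythmic addition or further VT procedure. Show these events and any ICD reprogramming on the patient's time line.
3. **Replace the yes/no drug item.** Use net change of the whole antiarrhythmic regimen from baseline at 6 and 12 months: reduced, unchanged or increased.

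**Cost.** This means rewording and a little more analysis. ICD records are scheduled at every time point and medication changes are already monitored. The assumption is that dates of drug changes, procedures and reprogramming can be taken from the records. The efficacy description may become less favourable. The rate up to first escalation can rest on a short period and tends to stop at a bad moment, because VT is what prompts escalation. It should therefore be shown beside the full-period rate and not in its place.
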